#### ❖ **Patient satisfaction in the perioperative period**

It will be assessed within 4 to 48 hours after surgery, before discharge, using the EVAN-G questionnaire (Auquier, Anesthesiology, 2005). This is a standardized and validated questionnaire, the purpose of which is to understand the experience of the perioperative period in a multidimensional way. It consists of 26 items structured in 6 dimensions called "Attention, Information, Intimacy, Pain, Comfort and Waiting Times". A global index is calculated as the sum of the dimensions. The scores of the dimensions as well as the overall index range from 0 (worst possible experience) to 100 (best possible experience).

### **7.4.5 Precautionary Principles in Women**

Since Fluorochol® and CISCholine® are not indicated for use in women, eligible women will be required to take a pregnancy test prior to the examination, which must be negative to meet the eligibility criteria.

In addition, any patient who has undergone a PET-choline examination with Fluorochol or CISCholine will be contacted the day after the examination by telephone: this protocol precaution is put in place to ensure the absence of adverse effects, in accordance with the biokinetics and rapid elimination of Fluorochol® or CISCholine® (approximately 12 hours).

### **7.4.6 Dosimetry**

The radiation reduction strategy is specified below during each of the two imaging examinations under study. Only patients for whom the first-line examination is negative or non-contributory will perform the 2 imaging examinations.

For FCH PET, the injected activity will be reduced from 3.5 MBq/Kg (standard dose for a FCH PET examination in oncology) to 1.5 MBq/kg, or approximately 105 MBq for a 70 kg patient. In return, the acquisition time will be increased to 5 minutes per step in list mode. According to the FCH dosimetry literature, the effective dose received is 0.018 mSv per MBq injected (Giussani, JNM 2012; ICRP, 2013). The irradiation associated with the injection of FCH in our study is therefore estimated at 1.89 mSv.

For the MIBI examination, the injected dose for the SPECT examination is 750 MBq of Sestamibi labelled with 99mTc. The effective dose received is 0.009mSv/MBq (see MA). The irradiation related to the injection for the SPECT is therefore 6.75mSv.

Each examination will be focused on the neck and upper mediastinum and the lenses will be excluded from the volume, in order to limit X-ray exposure. The dose-length product of a consecutive series of 31 patients of variable morphotype (body mass index range 15.4 to 38.1,

median 25.1) who underwent ENT-centered PET-CT in our PET unit was  $150.6 \pm 3.54$  mGy.cm, the expected CT dosimetry will be  $0.89 \pm 0.02$  mSv.

For the SPECT/CT, the dose received during the CT is about 50% more due to a 2-slice system instead of 64 on the CT of the PET. The dose received during the CT scan of the gamma camera is then of the order of 1.33mSv. The total effective dose of the two CT scans is in the order of 2.23mSv.

The total cumulative effective dose is therefore estimated to be 10.87 mSv.

**Radiation protection measures for patients** : As a precautionary measure, it is recommended that patients stay away from pregnant women and young children for an extended period of time for 12 hours after injection.

## 8 PHARMACEUTICAL FORM OF STUDY MEDICATIONS

### 8.1 MIBI

#### 8.1.1 Introduction to the RPM

**Technetium-99 m-labelled Sestamibi (2-methoxy-isobutyl-isonitrile)** is in the form of a radiopharmaceutical preparation kit, to be labelled with sodium pertechnetate (Tc99m) solution for injection. 99mTc period: 6.02 hours. Gamma-ray single-photon peak of 140 keV.

#### 8.1.2 Method of administration

Technetium-99-metastable labeled with sestamibi will be administered intravenously.

#### 8.1.3 Labelling

The dispensing label will include the following information:

- the name of the radiopharmaceutical preparation: 99mTc-sestamibi
- Study reference: APACH2
- the batch number;
- the activity;
- the volume;
- the exact date and time of measurement at the end of the preparation;
- the exact expiry date and time of use;
- the symbol indicating the presence of radioactive substances ("standard trisector").

#### 8.1.4 RPM Circuit for the Centre François Baclesse

- ✓ Reception: The Sestamibi® will be delivered, unmarked, to the airlock of the radiopharmacy of the François Baclesse Centre.
- ✓ Storage: The Sestamibi® should be stored in the refrigerator at 4°C
- ✓ Preparation: Preparation will be carried out in the low-energy leaded chamber, on the premises of the radiopharmacy (class D controlled atmosphere area, in accordance with Good Preparation Practices). The marking of Sestamibi®, using a 99mTc solution, will be carried out extemporaneously by a MER on the morning of the examination. A quality control will be carried out by the radiopharmacist to assess the quality of the marking. The product will be released if the Radiochemical Purity (PRC) is greater than 95%
- ✓ Method of dispensing: Once the preparation has been released by the radiopharmacist, the MER will prepare the patient's syringe taking into account the prescribed activity and the time of examination. The traceability of the dose (batch number, prescription number, patient identification, dose dispensed, dose administered, expiry date, etc.) will be carried out on the VENUS® nuclear medicine software (Nicesoft).
- ✓ Accounting allowing an assessment of compliance (accounting form): Given the radioactive nature of 99mTc-Sestamibi® (physical period 6.02h) and the single injection into the

department, compliance will be evaluated thanks to the traceability carried out on the nuclear medicine software VENUS® (Nicesoft).

### 8.1.5 RPM Circuit for Brest University Hospital

- ✓ Reception: The Sestamibi® kit will be delivered to the reception room of the nuclear medicine department of the Morvan Hospital of the Brest University Hospital
- ✓ Storage: The Sestamibi® kit will be stored at room temperature
- ✓ Preparation: The preparation will be carried out in the low-energy leaded chamber, on the premises of the radiopharmacy (class D controlled atmosphere area, in accordance with Good Preparation Practices). The marking of Sestamibi®, using a 99mTc solution, will be carried out extemporaneously by a MER on the morning of the examination. A quality control will be carried out by the laboratory technician or related technician, in order to evaluate the quality of the marking. The product will be released by the radiopharmacist if the Radiochemical Purity (PRC) is greater than 94%
- ✓ Method of dispensing and traceability: Once the preparation has been released by the radiopharmacist, the MER will prepare the patient's syringe taking into account the prescribed activity and the time of examination. The traceability of the dose (batch number, prescription number, patient identification, dose dispensed, dose administered, expiry date, etc.) will be carried out on the GERA® (Theleme) nuclear medicine business software in the first phase, followed by XPLORE® (EDL) in a second phase.

### 8.1.6 RPM Circuit for the Centre Eugène Marquis

- ✓ Reception: The Sestamibi® kit will be delivered to the reception room of the nuclear medicine department of the Eugène Marquis Centre in Rennes
- ✓ Storage: The Sestamibi® kit will be stored in a refrigerated 4°C-8°C chamber with continuously controlled temperature
- ✓ Preparation: Preparation will be carried out in the low-energy leaded enclosure, in the radiopharmacy premises (class D controlled atmosphere zone, in accordance with Good Preparation Practices). The marking of the Sestamibi®, using a 99mTc solution, will be carried out extemporaneously by a PPH or MER, the morning of the examination. A quality control will be carried out by a MER or a PPH, in order to assess the quality of the marking. The product will be released by the radiopharmacist if the Radiochemical Purity (PRC) is greater than 95%
- ✓ Dispensing method and traceability: Once the preparation has been released by the radiopharmacist, the MER or PPH will prepare the patient's syringe taking into account the prescribed activity and the examination time. Dose traceability (batch number, prescription number, patient identification, dose dispensed, dose administered, expiry date, etc.) will be carried out on the professional nuclear medicine software GERA® (Theleme).

## 8.2 FCH

### 8.2.1 Presentation of the RPM

The radionuclide fluorine-18 (fluoromethyl-(18F)-dimethyl-2-hydroxyethyl-ammonium) is presented as a solution for injection of F18-choline. It has a period of 109.8 minutes and emits positronic radiation of maximum energy 0.633 MeV, followed by annihilation photon radiation of 0.511 MeV.

### 8.2.2 Method of administration

The radionuclide will be administered intravenously.

### 8.2.3 Labelling

It will include the following information:

- • Name of preparation: F18-choline, solution for injection

- 474 - • Study reference: APACH2
- 475 - • Route of administration: IV
- 476 - • Batch number
- 477 - • Volume and activity administered
- 478 - • Name of Sponsor
- 479 - • Radioactivity pictogram

#### 480 **8.2.4 RPM Circuit for the Centre François Baclesse**

- 481 ✓ Reception: Fluorochol® will be delivered to the radiopharmacy airlock at the François
- 482 Baclesse Center like any radioactive medication.
- 483 ✓ Storage: Fluorochol®, for radiation protection and sterility purposes, will be handled in the
- 484 radiopharmacy preparation room in a leaded UNIDOSE® distribution enclosure (Trasis).
- 485 ✓ Preparation: Fluorochol® is a ready-to-use radiopharmaceutical specialty. Dispensing will
- 486 be carried out in the radiopharmacy premises (class D controlled atmosphere zone, in
- 487 accordance with Good Preparation Practices).
- 488 ✓ Dispensing method: The nominative dispensing of the dose to be administered will be
- 489 carried out using the UNIDOSE® dose distributor (Trasis). Dose traceability (batch number,
- 490 prescription number, patient identification, dose dispensed, dose administered, expiry date,
- 491 etc.) will be carried out on the VENUS® nuclear medicine software (Nicesoft).
- 492 ✓ Accounting allowing an evaluation of compliance (accounting form): Taking into account the
- 493 radioactive nature of Fluorochol® (physical period 110 minutes) and the single injection in
- 494 the department, compliance will be evaluated thanks to the traceability carried out on the
- 495 VENUS® nuclear medicine software (Nicesoft).

#### 496 **8.2.5 RPM Circuit for Brest University Hospital**

- 497 ✓ Reception: CISCholine® will be delivered to the nuclear medicine department of the
- 498 Morvan hospital at the Brest University Hospital like any fluorinated radioactive drug.
- 499 ✓ Storage: CISCholine®, for radioprotection and sterility purposes, will be handled within the
- 500 radiopharmacy preparation room in a TEMA SINERGIE class A leaded enclosure equipped
- 501 with a µDDSA® (TEMA SINERGIE) for dose distribution .
- 502 ✓ Preparation: CISCholine® is a ready-to-use radiopharmaceutical specialty. Dispensing will
- 503 be carried out in the radiopharmacy premises (class D controlled atmosphere zone, in
- 504 accordance with Good Preparation Practices).
- 505 ✓ Dispensing method: The nominative dispensing of the dose to be administered will be
- 506 carried out using the µDDSA® dose distributor (TEMA SINERGIE). The traceability of the
- 507 dose (batch number, prescription number, patient identification, dose dispensed, dose
- 508 administered, expiry date, etc.) will be carried out on the nuclear medicine software GERA®
- 509 (Theleme) initially then XPLORE (EDL) in a second step.
- 510 ✓ Accounting allowing an evaluation of compliance (accounting form): Taking into account the
- 511 radioactive nature of CISCholine® (physical period 110 minutes) and the single injection in
- 512 the service, compliance will be evaluated thanks to traceability carried out on the nuclear
- 513 medicine software GERA® (Theleme) firstly then XPLORE (EDL) secondly.

#### 514 **8.2.6 RPM Circuit for the Centre Eugène Marquis**

- 515 ✓ Reception: The CISCholine® will be delivered to the nuclear medicine department of the
- 516 Eugène Marquis Centre
- 517 ✓ Storage: For radiation protection and sterility purposes, the CISCholine® will be handled in
- 518 the PET preparation room in a single-dose® (Trasis) leaded distribution chamber.
- 519 ✓ Preparation: CISCholine® is a ready-to-use radiopharmaceutical specialty. The dispensing
- 520 will be carried out in a single-dose® (Trasis) leaded distribution chamber.

- ✓ Method of dispensing: The nominal dispensing of the dose to be administered will be carried out using the single-dose dose® distributor (Trasis). The traceability of the dose (batch number, prescription number, patient identification, dose dispensed, dose administered, expiry date, etc.) will be carried out on the GERA® nuclear medicine software (Thelem).

In the event of a failure of the TRASIS dose distributor, the dose is dispensed manually in the radiopharmacy preparation room in a LemerPax high-energy Class A leaded chamber.

## 9 MEDICO-ECONOMIC STUDY

The medico-economic analysis will be carried out from the point of view of health insurance. From this perspective, only direct hospital costs will be included in the analysis. They will include the costs of diagnosis, the costs of surgery (type of surgical procedure, duration of intervention and hospitalization, anesthesia) and the cost of possible complications (hematomas, infections, damage to the recurrent laryngeal nerve, chronic hypoparathyroidism).

The efficacy endpoint will be the cure rate at one month (normalization of serum calcium at one month post-surgery). An incremental cost-effectiveness ratio will be estimated to establish the average cost needed to cure an additional person by moving from the usual strategy to the new strategy.

A sensitivity analysis of the uncertain parameters of the model will be performed to test the robustness of the cost-effectiveness ratio.

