### 4.2 ORIGINALITY AND INNOVATION

In accordance with the recommendations on the methodology of evaluating diagnostic techniques (Rodger, Trials, 2012), we propose the first prospective randomized study comparing 2 diagnostic strategies (MIBI SPECT/CT or FCH PET/CT) first-line for the preoperative localization of PTA.

We seek to evaluate the best first-line diagnostic strategy to localize PTAs and guide surgery, at the lowest cost to society, by comparing the 2 strategies in terms of efficacy and cost of each strategy.

We hypothesize that FCH PET/CT will reduce the proportion of unnecessary invasive surgery decisions and that the higher cost of PET scan compared to MIBI will be offset by a lower cost in terms of the type of surgery performed correctly and complications.

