## 6.2 SECONDARY ENDPOINTS

The secondary endpoints are:

- Average cost of caring for a patient for each of the two strategies
- Sensitivity, specificity, error rates, positive and negative likelihood ratios of FCH PET/CT and MIBI SPECT/CT
- Rate of minimally invasive surgeries and bilateral cervical explorations for each diagnostic strategy
- Number of failures of parathyroid surgery (regardless of the type of surgery performed), defined by the persistence of primary hyperparathyroidism 6 months after surgery
- Complications occurring within one month of surgery: infections, hematomas, laryngeal recurrent nerve injury
- Cohen's kappa coefficients between the 2 independent readers, during their first reading, then during their second reading (3 months later); as well as between the first and second reading of each of the 2 readers
- Serum PTH concentration at baseline
- To compare detection sensitivities of FCH PET-CT at 10 min and 60 min post-injection, as well as semi-quantitative analysis.
- Scores for the 6 dimensions (comfort, attention, information, pain management, waiting times, intimacy) of the EVAN-G questionnaire administered perioperatively (4 to 48 hours after the intervention before discharge from hospitalization)

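### The cost-effectiveness ratio takes cure from calcium at one month although the trial judges surgical failure at 6 months, and it costs a chronic complication that no endpoint defines

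*Protocol*

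**What the plan says.** **Economic analysis (Protocol, section 9).** The viewpoint is declared: "The medico-economic analysis will be carried out from the point of view of health insurance". The cost scope follows: "From this perspective, only direct hospital costs will be included in the analysis". The listed costs include "the cost of possible complications (hematomas, infections, damage to the recurrent laryngeal nerve, chronic hypoparathyroidism"). The effect is stated thus: "The efficacy endpoint will be the cure rate at one month (normalization of serum calcium at one month post-surgery"). PTH plays no part in it. The ICER is interpreted as the average cost of curing one more person. A sensitivity analysis is planned on uncertain model parameters, none of which is named. No end date is given for costs.

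**Trial endpoints (section 6.2).** Surgical failure is "defined by the persistence of primary hyperparathyroidism 6 months after surgery". The complication endpoint reads: "Complications occurring within one month of surgery: infections, hematomas, laryngeal recurrent nerve injury".

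**Definitions of cure.** The synopsis requires normal calcium and PTH at both 1 and 6 months. Section 6.1 requires normal calcium at one month, and section 11.1 also places cure at one month.

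**Data collection.** Section 7.4.3 schedules calcium and PTH at 1 and 6 months. The flow chart (section 3) marks blood tests and adverse events at both visits. Section 10.3.1 limits adverse-event recording to 30 days after the last study drug. Section 7.4.3 allows surgery up to 12 weeks after the last scan.

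**Rationale.** Section 4.2 looks for the best strategy to "guide surgery, at the lowest cost to society", and section 4.3 speaks of a lower cost to the community.

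**The concern.** A ratio described as cost per additional cure should count as cured the patients whom the trial itself regards as cured. Section 9 uses an earlier and looser test than the 6-month failure endpoint, so the two can classify the same patient in opposite ways. The trial would then report a surgical failure in one table and an economic success in another.

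The second problem is on the cost side. Chronic hypoparathyroidism is to be costed, but the protocol neither defines it nor includes it in an endpoint, and its statements on how long adverse events are recorded disagree. Cases could be costed incompletely or differently between centres.

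The medico-economic comparison is the first secondary objective listed in section 5.2. What is at stake is its interpretation. The primary test is not affected.

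**Working it through.** **1. Figures available.** Section 9 states no cure rate, cost or ICER, so there is no economic figure to reproduce. The only calculable figure is the trial size in section 11.1: 60% against 90%, one-sided 5%, pooled variance without continuity correction. This gives 25 per arm with 80.4% power, as stated. It serves here only to show the weight of one patient: 1/25 = 4.0 points of an arm's cure rate, or 1/29 = 3.4 points if all 58 included patients are counted.

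**2. Who is classified differently.** Take calcium at one month (section 9) against disease status at 6 months (section 6.2):

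| Calcium at 1 month | Disease at 6 months | ICER | Section 6.2 |
|---|---|---|---|
| Raised | Persistent | Not cured | Failure |
| Normal | Absent | Cured | Not a failure |
| Normal | Persistent | **Cured** | **Failure** |

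The conflict at issue is the last row. A patient still hypercalcaemic at one month is already not cured in the ICER.

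**3. Effect on the ICER (illustrative, assumed rates).** Let one-month cure be c0 = 0.90 (standard) and c1 = 0.95 (experimental). Let f0 and f1 be the fractions of those patients with persistent disease at 6 months. Six-month cure is e = c × (1 − f). With the cost difference held fixed, the 6-month ICER divided by the one-month ICER is (c1 − c0)/(e1 − e0).

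| f0 | f1 | e0 | e1 | e1 − e0 | Ratio |
|---|---|---|---|---|---|
| 2% | 2% | 0.882 | 0.931 | 0.049 | 1.02 |
| 5% | 5% | 0.855 | 0.9025 | 0.0475 | 1.05 |
| 5% | 2% | 0.855 | 0.931 | 0.076 | 0.66 |
| 2% | 5% | 0.882 | 0.9025 | 0.0205 | 2.44 |
| 5% | 0% | 0.855 | 0.950 | 0.095 | 0.53 |
| 0% | 5% | 0.900 | 0.9025 | 0.0025 | 20 |

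Equal late failure changes little. Unequal late failure multiplies the ICER by 0.53 to 20 in these scenarios. The 20 reflects a denominator close to zero (0.05/0.0025) and is not a forecast.

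**4. Can chronic hypoparathyroidism be captured?**

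- Complication endpoint: three named events, ending at one month. Hypoparathyroidism is not among them.
- Adverse-event window: section 8 treats the two imaging agents as the study medications. If surgery falls s days after the last scan, recording under section 10.3.1 continues for 30 − s days after surgery. At the permitted maximum of 12 weeks (s = 84), 30 − 84 = −54, so the window closed 54 days before the operation. Even at s = 0 it ends 30 days after surgery.
- Flow chart: adverse events are marked at 1 and 6 months, which conflicts with that window.
- Blood tests: calcium and PTH at 6 months are scheduled, so the raw data should exist. What is missing is a definition and a rule that turns the results into a costed case.

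**The case against.** The best defence is that section 9 agrees with the body of the protocol: sections 6.1 and 11.1 also place cure at one month. Six-month failure is reported separately by strategy, so late failures are not hidden, and the planned sensitivity analysis could include a 6-month effect. The first two statements are true, but they leave the ICER in conflict with section 6.2 and with the synopsis. The sensitivity analysis as described commits to no such scenario.

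It can also be said that hypoparathyroidism is identifiable from the scheduled blood tests and the flow-chart visits, that abnormal laboratory findings are adverse events under section 10.2.1, and that related late serious events are reportable without time limit under section 10.3.2. This stands as far as raw data go. A reader might infer that the trial would record the complication as zero whatever its true rate. The documents do not support that: the event is absent from an endpoint list, which is a different matter.

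Three other inferences go too far:

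- **That all patients with persistent disease at 6 months are scored as cured.** Only those with normal calcium at one month are.
- **That one or two patients would reverse the sign of the incremental effect.** This requires cure rates close together in the two arms. The protocol states no overall cure rates; its 60% and 90% refer to the composite primary endpoint.
- **That costs and effect run over different periods.** Section 9 states no period for costs, so this cannot be shown.

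Finally, a reader might infer that the analysis fails because it cannot support a claim about cost to society. That wording belongs to the rationale. Section 9 openly declares a health-insurance viewpoint, which is legitimate, and although "only direct hospital costs will be included in the analysis" is a narrow scope, it is disclosed. No endpoint promises a societal result.

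**Conclusion.** The point holds in limited form. As written, the ICER gives hospital cost per additional patient with normal calcium at one month. It is described as cost per additional cure, and it disagrees with the 6-month failure endpoint for patients who are normal early and have persistent disease later.

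The number of such patients is unknown. Under the assumed 90% and 95% one-month cure, the effect on the ICER is about 2–5% if late failure is 2–5% in both arms. It can be large only if late failure differs between arms, and nothing in the protocol says whether it will.

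Chronic hypoparathyroidism is a cost item without a definition or an endpoint, and the recording rules around it conflict. The difference in wording between sections 4.2/4.3 and section 9 is a minor matter of alignment. The change is worth making because it is cheap and uses data already planned.

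**What to change.** 1. In section 9, define the economic effect as absence of persistent hyperparathyroidism at 6 months, which is the section 6.2 failure endpoint reversed, and state the laboratory criterion.
2. State the cost period: hospital costs from the first scan to 6 months after surgery.
3. Keep the one-month calcium result as a secondary economic analysis, consistent with section 6.1. Settle this together with the conflict between the synopsis and section 6.1 on the definition of cure.
4. Define hypoparathyroidism from the scheduled 6-month calcium and PTH, and report it as a complication so that the costed event is also a counted event.
5. Reconcile the recording window in section 10.3.1 with the adverse-event row of the flow chart. Also align section 7.4.4, which places the return visit between 1 and 6 months, with the two visits in section 7.4.3.
6. As a minor edit, match the society and community wording in sections 4.2 and 4.3 to the scope declared in section 9.

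The cost is protocol wording and a longer costing window. No visit or blood test is added. The one statistical drawback is slightly more missing data at 6 months than at one month; the one-month secondary analysis gives a check on this.

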## 4 SCIENTIFIC RATIONALE OF THE STUDY

### 4.1 BACKGROUND

Primary hyperparathyroidism is a common endocrine disease, related to autonomic overproduction of parathyroid hormone (PTH), usually by a parathyroid adenoma (PTA). The diagnosis is confirmed by a laboratory test. Excision of PTA remains the only curative treatment: despite a diagnosis often at an asymptomatic stage, normalization of hypercalcemia by excision of PTA improves bone mineral density and quality of life of patients. Bilateral cervical exploration of the parathyroids is now supplanted by minimally invasive surgery requiring precise localization of the PTA preoperatively. This minimally invasive technique, usually performed on an outpatient basis under local anesthesia, is associated with a better cure rate and fewer complications than bilateral cervical exploration, and at a lower cost (Udelsman-2011).

The current diagnosis to localize PTA is based on Tc99m-sestaMIBI (MIBI) scintigraphy with tomographic acquisition and CT scanning, negative in 33% of cases, leading to the proposal of bilateral cervical exploration (Ciappuccini-2012).

The recent literature and the results of our prospective APACH1 study (NCT02432599) strongly suggest the best diagnostic value of positron emission tomography coupled with F18-choline (FCH) CT scanning. Out of 25 patients with primary hyperparathyroidism and a negative MIBI scan, second-line FCH PET/CT was positive in 19 patients guiding parathyroidectomy and successfully reduced operative time in the majority of patients (Quak-2017).

Although FCH PET/CT is not yet used as a first-line treatment for primary hyperparathyroidism (cost of examination, availability of PET cameras, lack of marketing authorization for FCH in this indication), its contribution to guiding the surgical procedure seems promising. It therefore seems interesting to question the place of FCH PET-CT as a first-line imaging technique to localize PTA in biologically confirmed primary hyperparathyroidism, while taking into account the costs.

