### 265 **7.4.2 Randomization procedure**

266 After obtaining the patient's consent by signing the study consent, verifying the selection criteria  
267 and carrying out the inclusion assessment, randomization will be carried out.

268 Randomization will be performed on software dedicated to the study via a web portal.

269 Eligible patients will be randomized to one of two strategies:

- 270 •Standard arm: MIBI SPECT/CT and then, if negative, FCH PET/CT scan.
- 271 •Experimental arm: FCH PET/CT scan, and then, in case of negativity, a MIBI SPECT/CT.

272 An identification number will be assigned to the patient and will be used throughout the study.

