#### ❖ **Surgical decision for each diagnostic strategy**

In case of positive results of the first and/or second exam, the surgery will consist of a minimally invasive procedure, on an outpatient basis.

In case of negative imaging results (MIBI and FCH), an exploration of the 4 parathyroid sites will be performed.

In the case of multiple or ectopic PTAs, the surgical procedure will be adapted.

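### The two arms share one surgical rule, so planned exploration is expected to be equal by arm; the surgery-type cost offset can hardly appear, and cost per extra cure has a small, imprecise denominator

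*Protocol*

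**What the plan says.** The arms are set out in section 7.4.2: "Standard arm: MIBI SPECT/CT and then, if negative, FCH PET/CT scan" and "Experimental arm: FCH PET/CT scan, and then, in case of negativity, a MIBI SPECT/CT". Section 7.4.4 then applies one surgical rule to both: "In case of positive results of the first and/or second exam, the surgery will consist of a minimally invasive procedure", and "In case of negative imaging results (MIBI and FCH), an exploration of the 4 parathyroid sites will be performed". Surgery is adapted for multiple or ectopic adenomas.

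Section 4.2 hypothesises that "FCH PET/CT will reduce the proportion of unnecessary invasive surgery decisions" and that the higher price of PET will be recovered through the type of surgery and complications. Section 4.3 repeats this for first-line FCH. The pathway described in 4.1 differs from the standard arm: MIBI is "negative in 33% of cases, leading to the proposal of bilateral cervical exploration", with no FCH scan in between.

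Section 9 takes cure at one month (normal serum calcium) as the effect, whichever scan or operation led to it. It plans an incremental cost-effectiveness ratio to "establish the average cost needed to cure an additional person by moving from the usual strategy to the new strategy", plus a sensitivity analysis of uncertain model parameters. Section 6.2 lists mean cost per strategy and "Rate of minimally invasive surgeries and bilateral cervical explorations for each diagnostic strategy" as secondary endpoints.

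**The concern.** The economic hypothesis needs the arms to differ in type of surgery, but the pathway gives every patient with a negative first scan the other scan before exploration is planned. The comparison that would show a large drop in exploration is FCH against the pathway of 4.1. The standard arm is not that pathway, because it already contains a second-line FCH scan.

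Two consequences follow for the first-listed secondary objective. Similar exploration rates by arm could be read as evidence that FCH does not reduce exploration, when the pathway leads one to expect similarity. And the ratio in section 9 divides by a difference in cure that is expected to be small and is estimated from about 25 patients per arm, so its sign and size would be unstable.

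**Working it through.** **The plan's own figure.** The economic section states none. The sample size in 11.1 (60% vs 90%, one-sided 5%, power 80%) reproduces with the pooled-variance formula: [1.645 × √(2 × 0.75 × 0.25) + 0.842 × √(0.60 × 0.40 + 0.90 × 0.10)]² / 0.30² = 24.7, so 25 per arm. The sample size is not in question. It is set for an endpoint that credits first-line imaging only.

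**Step 1: planned exploration by arm.**
- Standard arm: P(MIBI negative) × P(FCH negative given MIBI negative).
- Experimental arm: P(FCH negative) × P(MIBI negative given FCH negative).
- Both equal P(both negative), provided a scan's result does not depend on its position in the sequence.
- Inputs from 4.1: MIBI negative in 33%; FCH positive in 19 of 25 MIBI-negative patients, so negative in 6/25 = 24%.
- Result: 0.33 × 0.24 = 7.9% in each arm, about 2 of 25. Expected difference: 0.
- Range: with 40% MIBI-negative (the complement of the 60% in 11.1), 0.40 × 0.24 = 9.6%. With 33% MIBI-negative and an assumed 10% FCH-negative among them, 3.3%. The rate is the same in both arms each time.

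**Step 2: the contrast the hypothesis needs.** If a negative MIBI led straight to exploration, as in 4.1, the comparison would be 33% vs 7.9%, about 25 points. The randomised arms do not estimate this.

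**Step 3: the remaining route to a difference in cure.** A positive first scan ends the work-up, so a false-positive first scan can change the outcome.
- Upper limit for MIBI from the protocol's percentages: 100 − 33 negative − 60 correctly guided = 7%.
- Assumed cure: 97% after true-positive focused surgery, 95% after exploration.
- Extreme case (7% false positives with MIBI, none with FCH, none of these patients cured):
  - standard arm (1 − 0.0792 − 0.07) × 0.97 + 0.0792 × 0.95 = 90.1%
  - experimental arm (1 − 0.0792) × 0.97 + 0.0792 × 0.95 = 96.8%
  - difference about +7 points.
- If 95% of the false-positive patients are cured, the difference is +0.1 point. With equal false-positive rates it is 0. With 3% for MIBI and 7% for FCH, none cured, it is −4 points.

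**Step 4: precision of the denominator.** The cure rates are assumptions, because the protocol gives none. The two sizes are the 25 evaluable and 29 included (58/2) per arm. At 95% in both arms, SE = √(2 × 0.95 × 0.05 / n) = 6.2 points (n = 25) or 5.7 points (n = 29). Binomial probabilities for the observed difference:

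| True cure, standard vs experimental | n per arm | P(zero) | P(negative) | P(zero or negative) |
|---|---|---|---|---|
| 95% vs 95% | 25 | 27% | 36% | 64% |
| 95% vs 95% | 29 | 25% | 37% | 63% |
| 95% vs 97% | 25 | 30% | 22% | 52% |
| 95% vs 97% | 29 | 27% | 22% | 49% |
| 90% vs 97% | 25 | 15% | 8% | 23% |
| 90% vs 97% | 29 | 13% | 8% | 20% |

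Row sums are taken before rounding. A zero difference leaves the ratio undefined. A negative one reverses its meaning. Even at 90% vs 97%, one-sided 5% power for the cure difference is 26% (n = 25) or 29% (n = 29).

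**Step 5: what still differs in cost.** Per 100 patients, the standard arm uses 100 MIBI and about 33 FCH scans. The experimental arm uses 100 FCH and, assuming FCH is negative in 10%, about 10 MIBI scans. This difference is measurable.

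**The case against.** The surgical rule fixes the planned operation, not the one performed. Tissue is examined during surgery (7.4.3), surgery is adapted for multiple or ectopic adenomas (7.4.4), and 7.4.6 triggers the second scan after a non-contributory first scan as well as a negative one. A reader might infer that exploration rates must come out equal; the documents support only equal expected rates of planned exploration. Adapted surgery should balance by randomisation, but false-positive first scans need not.

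A reader might also infer that the cost-offset hypothesis cannot be tested at all. That goes too far. Mean cost per strategy is its own endpoint, and section 9 counts diagnosis, procedure, duration and complications, so second scans avoided, operating time and complications can all be compared. Sections 4.2 and 4.3 also speak of surgical decisions, and the primary endpoint does assess decisions guided by the first-line scan. Only the offset through planned type of surgery is largely designed out.

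Nor do the documents show that the ratio divides by essentially zero. The probabilities in the working rest on assumed cure rates and fall to 20-23% at 90% vs 97%.

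The 7.9% multiplies two populations: the 24% comes from the sponsor's earlier study, whose title in section 16 limits it to patients with ultrasound and MIBI negative or inconclusive, while the 33% is a general MIBI-negative rate. The figure is an illustration; the symmetry does not depend on it.

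Replacing cure by the primary endpoint is tempting, but it would set whole-pathway costs against an effect that scores patients localised by the second scan and then cured as failures. Cure is a defensible measure for a health insurer.

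Finally, bootstrap detail can belong in an analysis plan that is not shown, and its absence is not the point here. The point is that the protocol fixes the ratio as its named result and states a hypothesis that does not match its arms. 'Usual strategy' can fairly be read as the standard arm, but 4.1 leaves another reading open.

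**Conclusion.** The point holds in a limited form. With the same rule in both arms, the expected rate of planned exploration is equal (roughly 8% each), assuming scan results do not depend on order. The surgery-type part of the offset hypothesis can reach the arm comparison only through false-positive first scans, worth at most about 7 cure points under extreme assumptions and possibly nothing, or a few points in the other direction. The cost-per-cure ratio is therefore likely to be unstable: a zero or negative denominator has a probability between about one in five and nearly two in three over the assumed cure rates. Total cost by arm, the primary endpoint and the sample size are unaffected. This is worth correcting because it concerns a secondary objective that can be made interpretable with data already planned.

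**What to change.** 1. **Section 9:** keep cure as the effect measure. Make the cost difference and incremental net benefit, with a joint (bootstrap) cost-effect interval, the main presentation. Give the cost-per-cure ratio second, and cost per patient appropriately guided by first-line imaging as a supplementary result.
2. **Section 6.2:** also report minimally invasive and bilateral rates by the decision that first-line imaging alone implies. State that equal rates of planned exploration are expected by design.
3. **Section 9, comparator:** state that the usual strategy means the standard arm (MIBI, then FCH if negative). If the pathway of 4.1 is the intended comparator, add a modelled scenario in which a negative MIBI leads to exploration, labelled as modelled.
4. **Sections 4.2 and 4.3:** restate the offset hypothesis to match the randomised arms.

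None of this changes patient care or data collection. The cost is some extra analysis and a headline less simple than a single cost-per-cure figure.
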